|                          |                                                                                                                                                                                                                                                                                                                                                                                                                                                       |
|--------------------------|-------------------------------------------------------------------------------------------------------------------------------------------------------------------------------------------------------------------------------------------------------------------------------------------------------------------------------------------------------------------------------------------------------------------------------------------------------|
|                          | 
For rupture rate Extended Mantel-Haenszel method including centre, treatment and time between open flexor tendon injury and surgery (-4 days, >4 days) will be used.
 
All other safety variables will be presented descriptively only.
                                                                                                                                                                                                |
| Study reporting          | 
After all patients have completed the 12-week visit, a report on blinded data will be produced. Only groups of patients will be displayed and no treatment code will be revealed in the report. The analyses will be performed by a study independent statistician. Meanwhile, the study will continue until all patients have completed the 12-month visit. After the last follow-up at 12 months, a more substantial report will be written.
 |
| Planned study time table | 
First Patient enrolled Q4 2009
 
Last Patient out Q1 2012
                                                                                                                                                                                                                                                                                                                                                                                 |

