| Investigational medicinal product, dose, and administration | PXL01 is a synthetic peptide sequentially derived from human lactoferrin. PXL01 20 mg/ml is formulated in a viscous solution of 15 mg/ml sodium hyaluronate. The drug product is administered locally between the flexor tendon and the tendon sheath and around the tendon sheath at a volume of 0.5 ml. Administration of the product is carried out after repair of the flexor tendon but before closure of the surgical wound.                                                         |
| Name of active ingredient                                   | PXL01                                                                                                                                                                                                                                                                                                                                                                                                                                                                                      |
| Number of patients                                          | According to the patient number calculations, 110 evaluable patients are needed. To adjust for withdrawals, 138 patients will be included in the study. A recalculation of the patient number will be made in connection to the planned blinded interim analysis, which will be performed when 69 patients (50%) have completed the 12-week visit. If the calculations suggest a patient number adjustment, a study protocol amendment will be submitted to the MPA.                       |
| Number and name of study sites                              | The following three sites will include the patients in this study:

 
1. [name], Dept. of Hand Surgery, Uppsala University Hospital, Uppsala, Sweden
 
2. [name], Dept. of Hand Surgery, Malmö University Hospital, Malmö, Sweden
 
3. [name], Dept. of Hand Surgery, Sahlgrenska University Hospital, Gothenburg, Sweden
 
4. [name], Dept. of Hand Surgery, Södersjukhuset, Stockholm, Sweden
 
 |

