| Study design and procedures | 
This is a multi-centre, randomised, double-blind, parallel study comparing PXL01 and placebo. Patients admitted for flexor tendon repair in zone I or II are screened for inclusion.
 
The patients will undergo 7 visits within the time frame of the study. In addition, two follow-up visits will be performed.
 
Visit 1: Screening/Surgery/IMP administration/post-surgery (Informed consent, demography, medical history, general injury characteristics, pregnancy test, vital signs, safety laboratory, eligibility criteria, specific injury characteristics, surgery, randomisation, IMP administration, concomitant medications, AE/SAE)
 
Visit 2: 1-5 days after IMP administration (QoL, mobilisation exercises, concomitant medications, AE/SAE)
 
Visit 3: 2 weeks after IMP administration (vital signs, safety laboratory, examination of the surgical area, tendon rupture, mobilisation exercises, mobilisation compliance, concomitant
                                                                                                                                                                                                                                                                                             |

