|                    | 
medications, AE/SAE)
 
Visit 4: 4 weeks after IMP administration (examination of the surgical area, TAM, DIPAM, tip-to-crease, TPM, tendon rupture, mobilisation exercises, mobilisation compliance, concomitant medications, AE/SAE)
 
Visit 5: 6 weeks after IMP administration (see Visit 4)
 
Visit 6: 8 weeks after IMP administration (examination of the surgical area, TAM, DIPAM, tip-to-crease, TPM, tendon rupture, mobilisation exercises, mobilisation compliance, concomitant medications, AE/SAE)
 
Visit 7: 12 weeks after IMP administration (QoL, examination of the surgical area, TAM, DIPAM, tip-to-crease, TPM, sensory evaluation, tendon rupture, recommendation for tenolysis, mobilisation compliance, concomitant medications, AE/SAE)
 
Follow-up 1: 6 months after IMP administration (QoL, TAM, DIPAM, tip-to-crease, grip strength, TPM, sensory evaluation, tendon rupture, recommendation for tenolysis, concomitant medications, AE/SAE)
 
Follow-up 2: 12 months after IMP administration (QoL, TAM, DIPAM, tip-to-crease, grip strength, TPM, sensory evaluation, tendon rupture, recommendation for tenolysis, concomitant medications, AE/SAE)
 
Before any study-related assessment takes place, patients are given verbal and written information about the study and informed consent is achieved from the patient and/or legal guardian. The study should be carried out in accordance with the Clinical Study Protocol (CSP), ICH guidelines for Good Clinical Practice (GCP), and applicable regulatory requirements.
 |

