| Exclusion criteria  | 
 
1. Treatment with any investigational product within 4 weeks of study entry
 
2. Patients previously included in the study
 
3. Thumbs with complete or partial division of flexor pollicis longus (FPL)
 
4. Concomitant fracture(s) requiring immobilisation
 
5. Injuries with associated soft tissue loss
 
6. Severe crush injury
 
7. Palmar plate injury requiring immobilisation
 
8. Devascularisation/requirement of vascular repair
 
9. Joint injuries
 
10. Bilateral injuries
 
11. Previous flexor tendon surgery in the digit, which is to be treated with IMP
 
12. Reduced motion in the digit, which is to be treated with IMP, or the corresponding digit prior to the injury
 
13. Compliance with mobilisation protocol not expected
 
14. Alcohol or drug abuse
 
15. Severe intercurrent illness, which in the opinion of the Investigator, may put the patient at risk when participating in the study, or affect the patient's ability to take part in the study
 
16. Pregnant or lactating females
 
17. Fertile women who do not accept the consistent and correct use of highly effective methods of birth control defined as implants, injectables, combined oral contraceptives, intra-uterine device (IUD)s, sexual abstinence or vasectomised partner during the first two weeks post-surgery. A condom alone is not considered an acceptable method for birth control, not even together with spermicide.
 
18. Known allergy to any component of the study product or placebo
 
19. Patients suffering from: 
 
• Diabetes Mellitus patients where significant diabetic complications may delay healing according to the investigator's judgement
 
• Rheumatoid arthritis
 
 
 
20. Or patients treated with: 
 
• Systemic steroids within one month
 
• Immunosuppressive drugs within three months
 
• Daily use of NSAIDs within one week or occasional use within 8 hours
 
 
 
 |

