|  | 
The per protocol analysis set after 12 months (PPAS12m) is a subset of the FAS and will include all patients in the FAS who have completed the study until the last follow-up visit at 12 months with no major protocol violations.
 
The safety analysis set (Safety) for safety analyses will include all patients who have completed the flexor tendon surgery and received the study medication.
 
Primary objective:
 
Analysis of TAM2 at 12-week visit.
 
The null hypothesis to be tested is that there is no difference in TAM2 at 12 weeks after surgical procedure between patients treated with PXL01 and patients treated with placebo. The alternative hypothesis is that there is a difference between treatments.
 
The primary objective will be tested using analysis of covariance (ANCOVA) with TAM at 12 weeks and the corresponding TAM of the contralateral hand as baseline and also including factors for centre, treatment and time between open flexor tendon injury and surgery (-4 days, >4 days).
 
Secondary objectives:
 
The following secondary objectives will be analysed in a similar way as the primary objective:
 
 
• TAM2 at all time points except for 12 weeks
 
• TAM3 at all time points
 
• Total Active Motion in DIP joint (DIPAM)
 
• Grip strength
 
• Total Passive Motion (TPM2 and TPM3)
 
 
TAM2 and TAM3 over time will be analysed using a repeated measurements approach.
 
For tip-to-crease distance analysis of variance (ANOVA) including centre, treatment and time between open flexor tendon injury and surgery (-4 days, >4 days) as factors will be used.
 
For tenolysis recommendation Extended Mantel-Haenszel method including centre, treatment and time between open flexor tendon injury and surgery (-4 days, >4 days) will be used.
 
The DASH QoL will be analysed by Wilcoxon rank-sum test.
 
The following secondary objectives will be presented descriptively only:
 
 
• TAM2 graded according to Strickland's Original Classification System
 
• Sensory evaluation with Semmes-Weinstein monofilaments
 
 
Safety variables:
 |

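### The grip-strength ANCOVA, read as following the primary model, has no term for injury to the dominant hand, so this secondary comparison may lose some precision

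*Protocol*

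**What the plan says.** All of this is in the protocol's Study protocol in short.

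- **Schedule** (Study design and procedures). Grip strength appears only at Follow-up 1 and Follow-up 2. The first is "6 months after IMP administration (QoL, TAM, DIPAM, tip-to-crease, grip strength, TPM, sensory evaluation"; the second, at 12 months, has the same list. This text sets timing and says nothing about a model.
- **Primary model** (Statistical methods, primary objective). The test is "analysis of covariance (ANCOVA) with TAM at 12 weeks and the corresponding TAM of the contralateral hand as baseline", "also including factors for centre, treatment and time between open flexor tendon injury and surgery", with delay in two classes.
- **Grip model** (Statistical methods, secondary objectives). Grip strength is in the list introduced by "The following secondary objectives will be analysed in a similar way as the primary objective". No separate grip model is given.
- **Availability of the other hand** (Exclusion criteria). "Bilateral injuries" are excluded, so an uninjured hand is always there as a reference.
- **Visit 1**. The recorded items include "demography, medical history, general injury characteristics, pregnancy test", not itemised further. Hand dominance is not mentioned anywhere in the text shown, whether as covariate, stratification factor or recorded item. No grip measurement is listed before surgery.

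**The concern.** One model is carried over from joint motion to grip. For motion, the same digit on the other hand is a reasonable stand-in for the injured digit's normal range. For grip, the stand-in may be off in a direction that depends on the injury. If the dominant hand is the stronger one and is injured, the other hand understates its normal grip; if the non-dominant hand is injured, the other hand overstates it.

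A regression slope on contralateral grip corrects for how strong the patient is. It cannot correct for which side was injured, because patients with the same contralateral grip are shifted in opposite directions. That shift stays in the residual.

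What is at stake is the width of the confidence interval for one secondary variable at two visits.

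**Working it through.** **The plan's own figures.** None is given for grip. The only sample-size figures are that "110 evaluable patients are needed" and that 138 will be included. These agree with a 20% allowance (110/0.80 = 137.5, rounded up to 138), although no rate is stated. Only the 110 is used below.

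**Assumed inputs, none from the documents.** Mean grip 40 kg; recovery r = 0.85 of normal; share of dominant-hand injuries p = 0.5; residual SD σ of 15-30% of mean grip (6-12 kg); side difference δ of 0%, 5% or 10%; equal allocation.

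**Step 1: the shift.** Let b be underlying grip, and s = +1 if the dominant hand is injured, otherwise −1.

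- Injured hand = r·b·(1 + sδ/2) + error
- Contralateral hand C = b·(1 − sδ/2)

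Substituting for b, injured grip is about r·C·(1 + sδ). At equal C, the gap between dominant-hand and non-dominant-hand injuries is 2·r·δ·C:

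- δ = 5%: 2 × 0.85 × 0.05 × 40 = 3.4 kg
- δ = 10%: 2 × 0.85 × 0.10 × 40 = 6.8 kg

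The shift enters outcome and covariate in opposite directions, so the gap is about twice the side difference.

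**Step 2: variance inflation from omitting the factor.** Inflation = 1 + gap²·p(1−p)/σ². For example, with δ = 10% and σ = 6 kg: 1 + 6.8² × 0.25/36 = 1.321. Fitting the factor costs one degree of freedom. With 110 patients and 7 parameters already fitted, that is about 1/(110 − 7), or 1%, so the net ratio is about 0.99 times the formula.

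**Step 3: simulation of the stated ANCOVA** (110 patients, 4 centres, delay factor, contralateral grip; 4,000 runs per scenario). The ratio is the variance of the treatment estimate without the dominance term over that with it.

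| δ | σ | Formula | Formula × 0.99 | Simulated ratio |
|---|---|---|---|---|
| 0% | 6-12 kg | 1.000 | 0.99 | 0.99-1.00 |
| 5% | 6 kg | 1.080 | 1.07 | 1.06 |
| 5% | 12 kg | 1.020 | 1.01 | 1.00 |
| 10% | 6 kg | 1.321 | 1.31 | 1.30 |
| 10% | 12 kg | 1.080 | 1.07 | 1.06 |

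Formula and simulation agree. A rougher calculation that takes full recovery (r = 1) and ignores the degree of freedom gives 1.03-1.11 at 5% and 1.11-1.44 at 10%. Those upper ends are too high for the assumptions above.

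**Step 4: a second set of assumptions.** Normal grip 40 kg (SD 10), recovery 85% (SD 10-20 points), measurement SD 3 kg and 40-50% dominant-hand injuries. Adding the factor cuts residual variance by 3.0-7.6% at δ = 5% and 10.3-23.9% at δ = 10%. At 110 patients the variance ratios are 1.02-1.07 and 1.10-1.31.

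**Step 5: validity.** Under no treatment effect, the mean estimate from the model without the term stayed within about 0.06 kg of zero, and type I error was 4.4-5.3%.

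**Step 6: what the loss is worth.** Across both sets the variance is larger by 0-7% at δ = 5% and 6-31% at δ = 10%.

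- In patients: 110/1.07 = 103 at worst for 5%; 110/1.31 = 84 to 110/1.06 = 104 for 10%.
- In power, for a comparison with 80% when the term is included (two-sided 5%): Φ(2.80/√1.07 − 1.96) = 77% at worst for 5%, and Φ(2.80/√1.31 − 1.96) = 69% at worst for 10%.

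**The case against.** The strongest objection is that this is SAP detail. Saying that grip is analysed similarly to the primary leaves room for another covariate, and the SAP was not among the documents. Almost every ANCOVA omits some prognostic factor, and under randomisation it is still valid. This stands to the extent that the protocol contains no error here. It does not dispose of the point: the protocol names a covariate and factors and extends them to grip, and a SAP can use dominance only if it was collected.

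Four stronger readings are tempting, and the documents do not support them.

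- **That a side difference in grip is established.** The protocol gives no side difference, grip mean or SD, and no share of dominant-hand injuries. At a difference of zero there is no loss.
- **That the protocol expressly adjusts grip for the other hand's grip.** The covariate it names is "the corresponding TAM of the contralateral hand as baseline", which is joint motion. Contralateral grip is the natural counterpart, but it is an inference.
- **That dominance is not recorded.** Visit 1 lists injury characteristics without itemising them, and this is a summary section. Its silence does not show that the item is uncollected.
- **That chance imbalance in dominant-hand injuries is a further harm.** It is the same effect as the lost precision, and the standard error already reflects it.

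**Conclusion.** The point holds as a minor, optional efficiency improvement to one secondary analysis. If the grip model mirrors the primary model, and if grip differs by hand dominance, the treatment comparison at 6 and 12 months is less precise than it need be. The variance is larger by about 0% with no side difference, 0-7% with 5% and 6-31% with 10%. The top of the last range needs a small residual SD. The conclusion rests on the inferred use of contralateral grip as covariate and on the assumed inputs listed in the working.

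A reader might infer that the grip result would be biased or its test invalid. It would not: randomisation protects the estimate, and simulated type I error is at its nominal level. The primary TAM2 analysis and the sample size are not affected.

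**What to change.** In the grip-strength ANCOVA only, keep contralateral grip as covariate, state that explicitly, and add one pre-specified two-level factor: injured hand dominant, yes or no. Confirm that dominance is recorded at Visit 1 and add the question if it is not. Fix the factor before unblinding so that it is not a data-driven choice. Leave the TAM and TPM models unchanged.

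The cost is at most one Visit 1 question, one degree of freedom (about 1% of variance if there is no side difference) and one line in the SAP. No extra patients, visits or procedures are needed.
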